#### Theoretical assumptions of the employed speech production task

We devised an eye-tracking experiment, consisting of two blocks, to verify the proposed cognitive account of advance planning of sentence intonation. The aim of the first block is to establish the tonal differences between short and long sentences when no additional cognitive load is imposed on speech production. For this block, participants are asked to describe monochromatic line drawings depicting an action involving three actors (Fig 2, for similar materials see [65]). Either one or two of the three actors can function as the initiator(s) or the recipient(s) of an action, i.e., agent or patient respectively. In other words, either role can be executed by one or multiple actors. In the case of multiple actors, the two actors may or may not share an identity (e.g., both are donkeys or one is a donkey and the other is a goat).

The concrete task setting ensures that the picture descriptions vary between short and long (e.g., ‘A man is pulling donkeys’ vs ‘A man is pulling a donkey and a goat’). As the length effect is sometimes reported to occur between the sentences consisting of short or long sentence-initial subject noun phrases (e.g., ‘*The man* is pulling the donkey’ vs ‘*The man and the woman* are pulling the donkey’), but to be absent between the sentences containing short or long sentence-final noun phrases (e.g., ‘The man is pulling *donkeys*’ vs ‘The man is pulling *the donkey and the goat*’) [4], the proposed experiment will control the sentence length at both of these syntactic positions. However, the methodological assumption is that the conceptual planning processes do not differ between the two conditions of multiple actors (two agents vs two patients) because the complex visual scenes are similar in that they require an early higher-level conceptual decision for encoding the relationships between the actors depicted [32, 65].

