**Fig 2 pone.0259343.g002:**
[figure not shown]
An example picture in four experimental conditions eliciting short and long sentences.

The aim of this fully crossed two-factorial design is to elicit transitive sentences that differ in length, such that the similar double actor condition elicits short sentences and the different double actor condition triggers speakers to produce long sentences. The concrete task setting will ensure that the picture description will indeed be either short or long. In particular, participants are asked to describe the pictures by mentioning all three actors. Moreover, they are trained to use either plural NPs for the actors sharing the identity (e.g., ‘donkeys’) and coordinated NPs for the actors differing in the identity (e.g., ‘a donkey and a goat’).

The complex two-by-two design is necessary for the manipulation of the length effect at the two syntactic positions. This means that either the sentential subjects of prospective sentences are short or long (e.g., Mees sikutab eesleid, ‘The man is pulling the donkey’ vs Mees ja naine sikutavad eesleid, ‘The man and the woman are pulling the donkey’), or the sentential objects vary between short and long (e.g., Mees sikutab eesleid, ‘The man is pulling donkeys’ vs Mees sikutab eeslit ja kitse, ‘The man is pulling the donkey and the goat’). This design allows researchers to control for the possible interactions between the prosodic phrasing and F0 declination [4], and observe the effect of cognitive load in a worst-case scenario where the pitch peaks do not increase together with the length of object NPs.

Altogether, 64 different pictures of simple events (target items) are created for the study (4*64 = 256 pictures in total). Another set of 84 pictures will serve as distractor items. The distractor items will depict a variety of transitive and intransitive events comprising one to four identifiable actors. Half of the pictorial items are combined with a verb probe task separated into a second experimental block.

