### Participants

Study subjects will be recruited from the university’s students and staff through informational mailing lists at the University of Tartu in Estonia. They must be native speakers of Estonian, and between 18 and 50 years old. The upper age limit is applied because the WM capacities are known to decay in ageing speakers (see in [65]) and due to the COVID-19 pandemic, in which the older participants belong to the higher risk group. Speakers eligible for the study should have normal or corrected to normal vision (soft contact lenses included, glasses excluded), no diagnosed language impairments and normal hearing ability. Subjects will be reimbursed 5 euros for their participation in the study.

Since the experiment is designed such that samples of subjects are going to respond to samples of target trials, PANGEA web application (Power Analysis for General ANOVA designs; [79] provided an *a priori* power analysis. The PANGEA analysis (variation parameters set to PANGEA defaults) indicates that, given the small to medium effect size (d = 0.45), the recommended sample size of 60 subjects is suitable for achieving the statistical power (1-*β*) of 0.8 in the evaluation of the three main effects and the three-way interaction between the fixed effects. Due to the spontaneous nature of the task, not all of the subjects will perform expectedly on all target trials. Therefore, the number of subjects is increased by approximately 33% of observations. Therefore, the resulting sample size is 84 subjects. The estimated sample size is at the limit of the feasibility of planned phonetic analyses and the project’s timeline.

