#### Statistical analysis

The goal of the statistical analyses is to determine whether the scaling of sentence-initial pitch peaks in long sentences is affected by an independent effect of incrementality or by the simultaneous effects of incrementality and high mental load. As the manipulations of the factors Double Actor (agent vs patient) and Identity (same vs different) elicit short and long sentences (see in Materials), the combinations of these are reduced into a factor Sentence Length (short vs long) for the main analysis. Thus, the main analysis examines the effect of the interaction between Cognitive Load (low vs high) and Sentence Length (short vs long) on (i) the proportional duration of naming gazes at the first-mentioned actors, (ii) duration of naming gazes, (iii) the sentence-final pitch valleys, (iv) and the sentence-initial pitch peaks.

The four dependent variables (duration of naming gazes, proportional gaze durations, sentence-final F0 minima, sentence-initial F0 maxima) are modelled with separate linear mixed-effects regression analyses (LMER, as implemented in the *lme4* package in [82, 85]). All models include the interaction between Cognitive Load (low vs high) and Sentence Length (short vs long) as the fixed effect, the block and trial number as the covariate effects, and random intercepts and slopes for items and subjects. The analysis will be carried out using sum-to-zero coding of the fixed effects. To avoid the convergence issues, the models will be optimized following the procedures suggested in Bates et al. [82]. First, the continuous variables block and trial are centred and/or scaled for the statistical analyses. Second, the convergence tolerances are adjusted by applying an optimizing algorithm diverging from the standard test but which results in the converging model. Third, and only in case the previous measures do not yield the convergence of the model fit, the random effects structure will be simplified by removing the correlations term from the random effects structure. Finally, the significances of the model estimates are obtained with the help of the *lmerTest* package [86] in R [85]. The significances of the main effects and the interaction are determined at the threshold of p<0.05.

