The exploratory analyses inspect the three-way interaction between the factors Double Actor (agent vs patient), Identity (same vs different) and Load (low vs high) on (i) the proportional duration of naming gazes at the first-mentioned actors (ii) and the sentence-initial pitch peaks. The first exploratory analysis of naming gazes aims to determine whether the pictorial scenes combining the similar and differing event participants either in agent or patient role would induce planning increments differing and gradually increasing in size. Known from the studies relying on the grouping effect (though with moving displays), the chunk conceptualized and planned before the speech onset increases together with the more complex phrase structures [37, 38]. The second analysis will assess whether the length-dependent pitch raising depends on the syntactic position of the length variation (as in [4]). If a large number of sentences will be uttered with a break between the subject noun phrase and the verb phrase, the desired significant interaction with Identity (i.e., Sentence Length) and Cognitive Load might only occur when Double Actor corresponds to the agent. The models of the exploratory analyses and the significance testing will follow the same procedures as described for the main analyses.

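### The main models leave out the crossed factor Double Actor, and the double-agent Load x Length contrast that the authors themselves anticipate for initial pitch peaks has only exploratory status

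*Protocol article*

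**What the plan says.** The Materials and Design sections set up a fully crossed design of Double Actor, Identity and Cognitive Load, with 8 pictures in each of 8 conditions per participant. The reason for varying Double Actor is given in the section on the theoretical assumptions of the speech production task: because the length effect is sometimes reported for subject phrases but not for sentence-final ones, "the proposed experiment will control the sentence length at both of these syntactic positions". Materials adds that the design lets the authors "observe the effect of cognitive load in a worst-case scenario where the pitch peaks do not increase together with the length of object NPs".

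In Statistical analysis, "the combinations of these are reduced into a factor Sentence Length (short vs long) for the main analysis". The model statement is: "All models include the interaction between Cognitive Load (low vs high) and Sentence Length (short vs long) as the fixed effect". Block and trial number are the only covariates. On coding: "The analysis will be carried out using sum-to-zero coding of the fixed effects". On testing: "The significances of the main effects and the interaction are determined at the threshold of p<0.05".

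Double Actor returns only in the exploratory analyses, as a three-way model for proportional naming-gaze duration and for sentence-initial pitch peaks. There the authors write that, if many speakers pause after the subject phrase, "the desired significant interaction with Identity (i.e., Sentence Length) and Cognitive Load might only occur when Double Actor corresponds to the agent".

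**The concern.** The design pays for a second length position, and the protocol names a scenario in which that position carries no effect. The main models then ignore which position was varied. Two separate things follow.

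- **Model specification.** Double Actor is controlled by the experimenter and changes both the picture and the sentence, yet no main model accounts for it. In the balanced design this costs precision only. After exclusions it can also bias the Length terms.
- **Status of the contrast.** The main Load x Length estimate is an average over positions. If the effect sits in subject position only, the main test may miss it, and the contrast that would show it can be reported only as exploratory. In a study registered before data collection, that status decides what may be claimed.

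**Working it through.** **1. The plan's own power figure.** Participants gives 0.80 power with 60 subjects at d = 0.45, with variation parameters at the software defaults. It gives this for the three main effects and the three-way interaction. The two-way Load x Length test is not named. The default variances are not stated, so the figure cannot be reproduced. A paired t-test with n = 60 gives 0.93. A crossed subject-and-item approximation gives 1.00 down to 0.76 as the assumed item-variance share runs from 0 to 0.40. The 0.80 used below for Load x Length is therefore an assumption.

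**2. Dilution of the averaged test.** Take a two-sided 5% level (sidedness is not stated). For base power P with an equal effect in both positions, the non-centrality is λ = z(0.975) + z(P) = 1.96 + 0.84 = 2.80. With equal cells, if the object-position effect is a fraction f of the subject-position effect, the averaged coefficient is multiplied by (1 + f)/2. Power is then approximately Φ(λ(1 + f)/2 − 1.96).

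| Object effect as fraction of subject effect | Non-centrality | Power |
|---|---|---|
| 1 | 2.80 | 0.80 |
| 1/2 | 2.80 × 0.75 = 2.10 | 0.56 |
| 1/4 | 2.80 × 0.625 = 1.75 | 0.42 |
| 0 | 2.80 × 0.5 = 1.40 | 0.29 |

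A simulation with 60 subjects, 8 trials per cell and 20,000 runs gave 0.28 to 0.29 for the last row.

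**3. Sensitivity to the assumed base, with f = 0.** Power falls from 0.70 to 0.24, from 0.90 to 0.37, from 0.95 to 0.44 and from 0.99 to 0.57. If all 84 subjects are usable and precision scales with subjects, λ = 2.80 × √(84/60) = 3.31, and power falls from 0.91 to 0.38.

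**4. Does adding Double Actor restore this power?** No. With balanced cells and sum-to-zero coding, the averaged Load x Length contrast is orthogonal to Double Actor and its interactions, so the estimate does not change. Power with f = 0 stays at about 0.29.

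**5. The double-agent contrast.** It has the full effect on half the trials. If trial noise dominates, the non-centrality is 2.80/√2 = 1.98 and power is 0.51. If subject-slope noise common to both positions dominates, power rises towards 0.80. The simulated settings gave 0.51 to 0.72. These values are at an unadjusted 5% level. With a level of 2.5% for each of two tests (critical value 2.24), the contrast has Φ(1.98 − 2.24) = 0.40 when trial noise dominates, and the main test with equal effects has Φ(2.80 − 2.24) = 0.71.

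**6. What the missing term does.** Double Actor varies within an item across lists, so its effect D falls into the residual when it is not modelled. If p is the share of double-agent trials retained in a cell, the Length estimate is shifted, to a first approximation, by D × (p_long − p_short). The Load x Length estimate is shifted by D times the difference of that gap between high and low load. Both shifts are zero in the balanced design. Pre-processing and data harvesting removes trials for late first fixations, track loss, disfluency, non-transitive structure and long latencies, and nothing keeps the shares equal after that. The documents give no D and no loss by condition, so this part cannot be given a size.

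**The case against.** Pooling follows from the protocol's theory. The hypothesis concerns the number of concepts held in working memory, and the speech production task section assumes that conceptual planning does not differ between double agents and double patients. On that view, the averaged Load x Length effect is the right target. The absence of an object-position effect is only a possibility, tied to frequent pauses after the subject phrase; the contrary study cited used read German, not spontaneous Estonian. The exploratory section already plans the three-way model for initial pitch peaks, states its purpose and direction, and uses the same fitting and testing procedures. Testing the general effect first and its dependence on position second is a normal order.

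Most of this stands. It supports keeping the averaged test as the main one, and it justifies pooling for the gaze outcomes, where only a Load effect is expected. It does not explain why a crossed design factor is absent from the models. The equal-planning assumption also does not settle the pitch outcome, where the protocol itself expects a possible difference by position.

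A reader might infer more than the documents support:

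- **That dropping Double Actor causes the power loss.** Step 4 shows that it does not.
- **That the main test has 29% power.** This needs an object effect of exactly zero and a 0.80 base that the protocol does not state for this test.
- **That position is never analysed.** It is, as an exploratory analysis for two outcomes.

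**Conclusion.** The point holds in two limited parts. First, all four main models omit a controlled, fully crossed factor. This leaves its variance in the residual and leaves the Length terms open to leakage once exclusions unbalance the cells. The direction is clear, but the size cannot be derived from the documents. Second, for sentence-initial pitch peaks, the double-agent Load x Length contrast that the authors themselves anticipate is exploratory only, while the main test averages over positions. On an assumed 0.80 base, the averaged test has about 0.56, 0.42 or 0.29 power when the object effect is a half, a quarter or none of the subject effect. The power argument applies to the pitch-peak analysis and not to the other three outcomes.

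**What to change.** Fit the main models with Load, Sentence Length, Double Actor and their interactions, sum-coded, with the convergence steps already planned. Keep the averaged Load x Length term as the main test. For sentence-initial pitch peaks, move the Load x Length contrast within double-agent pictures from the exploratory section to a pre-specified secondary contrast of the same model. State its place: tested after the main test, or multiplicity-adjusted with it. If the order is a strict gate, the contrast can never be significant more often than the main test, so with no object effect it is capped at about 0.29. An adjusted pair avoids that cap at some cost to the main test (step 5). Either way, only part of the loss is recovered.

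The change is to wording only and needs no new data. The costs are a somewhat larger model that may be harder to bring to convergence, and one more comparison to control.

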### Design

The two visual factors Double Actor and Identity, as well as the factor Cognitive Load, all comprising two levels, will be fully crossed, resulting in eight conditions in total. The two-level fixed effect Cognitive Load reflects whether the picture was described while maintaining a list of nouns in WM or not (levels low and high). The trials with no load constitute the first block of the experiment (32 target pictures) and the trials with the load (32 target pictures) constitute the second block.

Four lists of target trials are created by distributing the 256 target pictures between the four conditions (Double Actor crossed with Identity) using the Latin square approach. Target pictures in lists are distributed between the same set of 84 distractor pictures such that there are one or two distractor items for every target item, resulting in 148 experimental trials per list in total. Another set of four lists is created where the leftward placement of agents is reversed, resulting in eight lists. For the verb probe task, all eight lists are reversed for a further set of eight lists, amounting to 16 lists altogether. In all 16 lists, the second half of the trials include the verb probe task.

Participants are presented with all eight conditions across 64 target pictures (repeated measures, within-subject, between-item). The within-subject design is necessary because F0 tends to be highly variable and affected by many other, also non-linguistic, factors. The tonal differences between the conditions can most reliably occur within a speaker, ideally also within the items of the same speaker. Due to this practical limitation, most of the classical intonation research typically records all conditions for a speaker (see e.g., [4, 6–11, 46–49]). The within-item design is not optimal for the purposes of this study, as we aim to record genuine planning processes. Thus, the repeated measures design with within-subject and between-item factor represents the best fit between the purposes of the study and the limitations of the F0 measurements. In other words, the design resembles the ANOVA repeated measures design with a within-subject factor eliciting 64 measurements (8 images X 8 conditions) per participant.

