The first analysis tests the extent to which the proposed verb probe task tapped the conceptual retention. The proportional duration of naming gazes at the first-mentioned actors is assumed to increase under the high cognitive load. Thus, only the main effect of cognitive load is expected in this analysis. The second analysis investigates the absolute duration of naming gazes, as the interference effect may arise at the phonological planning stage (or semantico-syntactic encoding) instead. In particular, if the phonological encoding of the first-mentioned actors is disrupted due to the memorization of three words the duration of naming gazes right before the speech onsets should increase under the high cognitive load.

The third analysis checks the preliminaries of advance planning of sentence intonation. Namely, the aim is to test how constant the sentence-final low F0 is in the elicited sentences. For this, the statistical evaluation should find no effect of Sentence Length. Nevertheless, the sentence-final low F0 may increase under the high cognitive load, as the existing studies have reported generally higher and flatter F0 contours for speech under mentally challenging conditions [58–64].

Finally, the fourth analysis tests the effect of cognitive load on the scaling of sentence-initial pitch peaks. The significant interaction between Cognitive Load and Sentence Length should demonstrate that the degree of length-dependent pitch raise in sentence-initial pitch peaks depends on the cognitive load. If the cognitive load causes sentence planning processes to proceed incrementally and the incrementality of planning processes mainly bears on the scaling of the pitch peaks, then the sentence-initial pitch peaks are lower under the high load than under the low load, and the difference between the high and low load is greater in long sentences than in short sentences. If the incrementality and the high load both play a role in pitch scaling, then the tonal difference between the high and low cognitive load is expected to occur only in long sentences.

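### Every model contains both block and Cognitive Load, which are the same variable in this design, so the load main effect is not separable from block

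*Protocol article*

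**What the plan says.** The protocol article's Statistical analysis section states: "All models include the interaction between Cognitive Load (low vs high) and Sentence Length (short vs long) as the fixed effect". The same sentence enters that interaction "as the fixed effect, the block and trial number as the covariate effects, and random intercepts and slopes for items and subjects". On coding it says "The analysis will be carried out using sum-to-zero coding of the fixed effects", and as a first step against convergence problems "the continuous variables block and trial are centred and/or scaled for the statistical analyses". Main effects and the interaction are each tested at p<0.05. The exploratory models are to follow the same procedures.

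The Design section fixes the order of load: "The trials with no load constitute the first block of the experiment (32 target pictures"), and the 32 load targets make up the second. It adds: "In all 16 lists, the second half of the trials include the verb probe task". Half of the 16 lists are reversals of the others, which moves pictures between halves but never moves the load task. The Procedure section itself glosses block as low versus high load.

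For the first analysis, the check that the verb probe task taxed conceptual planning, the plan says: "Thus, only the main effect of cognitive load is expected in this analysis".

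**The concern.** A covariate can adjust a factor only if the two vary separately somewhere in the data. Here block equals 1 exactly when load is low and 2 exactly when load is high, for every subject and list. A model holding both has no unique estimate for either. The plan's convergence steps (centring, scaling, another optimiser, removing random-effect correlations) address a different problem and cannot cure this one.

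What depends on the load main effect:

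- **Analysis 1** rests on it entirely.
- **Analysis 2** predicts longer naming gazes under high load.
- **Analysis 3** allows for higher sentence-final F0 under high load.
- **Analysis 4** must tell two scenarios apart. In one, load lowers pitch peaks in short and long sentences, more so in long ones. In the other, it does so only in long ones. Both predict the interaction. The simple load effect in short sentences distinguishes them, and that is the load main effect plus or minus the interaction.

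Listing block as a covariate also suggests that order has been adjusted for, which this design cannot deliver.

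**Working it through.** **Design counts reproduced.** 32 + 32 = 8 × 8 = 64 targets per subject, and 64 + 84 distractors = 148 trials, as stated. Two equal halves give 74 trials per block.

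**Aliasing.** Code load as −1 (low) and +1 (high). Block is 1 or 2, so centred block is −0.5 or +0.5. Then centred block = 0.5 × load on every trial, and their correlation is 1.

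**Rank.** The matrix was built for 84 subjects × 64 targets = 5,376 rows, with columns intercept, Load, Length, Load × Length, block and trial.

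- There are 6 columns and the rank is 5. With block scaled to unit SD, the single null direction is Load against block (0.707, −0.707), with zero weight on all other terms.
- Load and block are each not estimable. Intercept, Length, Load × Length and trial are.
- This holds whether trial runs through the session or restarts in each block.
- In the exploratory three-way model, 8 factorial columns + block + trial = 10 columns, and the rank is 9.

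**Software behaviour.** On simulated data, lme4 reports a rank-deficient matrix and drops one column. With load first in the formula, block goes. With block first, the load main effect goes and its estimate appears under block, apart from sign and scale.

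**After deleting block.** The matrix has full rank (5 of 5). The load contrast still contains order: in one simulated data set with a pure second-block shift of 0.30 and no load effect, it came out at 0.29.

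**Trial number.** The article does not say how trial is numbered.

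- *Session-wide, 1–148.* Within-block variance = (74² − 1)/12 = 456.25. Between-block variance = 37² = 1369. Total = 1825.25. R² of load on trial = 1369/1825.25 = 0.75 (correlation 0.87), so the variance inflation is 1825.25/456.25 = 4.0. With targets at random positions the simulation gave 4.06. The standard error multiplier is √4 = 2.0 on the trial-noise part.
- *Within block, 1–74.* Both blocks have the same expected mean position, so the correlation is about 0 and the inflation about 1.0.
- Load × Length has inflation 1.00 under either numbering.

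**What an inflation of 4 costs.** Only trial-level noise is inflated, not by-subject variation in the load effect. Assume ±1 coding, ignore items, and let s be the by-subject load-slope variance as a share of slope plus residual variance. Per subject, the variance of the load difference is 4s + (1 − s)/16, which becomes 4s + 4(1 − s)/16. For a load effect that would have power 0.80 (noncentrality 2.80, two-sided 0.05, normal approximation):

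| s (assumed) | variance ratio | SE ratio | power |
|---|---|---|---|
| 0 | 0.2500/0.0625 = 4.00 | 2.00 | 0.29 |
| 0.05 | 0.4375/0.2594 = 1.69 | 1.30 | 0.58 |
| 0.10 | 0.6250/0.4563 = 1.37 | 1.17 | 0.67 |
| 0.20 | 1.0000/0.8500 = 1.18 | 1.08 | 0.73 |

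**The case against.** The strongest reply is that the plan lists the load terms before block. A formula typed in that order makes lme4 drop block, with a message, and the fitted model is then the one recommended here. The load coefficient is estimated, and aliasing by itself deflates nothing. That stands. It does not rescue the plan, because the model described is not the model fitted, and which term survives depends on an order the text does not fix.

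A reader might infer that the central test fails. It does not: the Load by Length interaction, which the plan names as the main analysis, is estimable with no inflation.

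A reader might also infer that power for load collapses from 0.80 to about 0.29. The article does not support that. The figure needs session-wide trial numbering, which is not stated, and no by-subject variation in the load effect, although the plan specifies random slopes for subjects.

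Nor is session-wide numbering an error. Its inflation is the price of adjusting load for linear drift, and within-block numbering gives that adjustment up.

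Finally, the text calls block continuous, which might hint at a finer index. Nothing else in the article supports that, and it describes exactly two blocks.

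**Conclusion.** The point holds in limited form. Every main and exploratory model as written is rank-deficient by exactly one column, because block and Cognitive Load coincide in all 16 lists. This follows from the stated design and needs no assumption about effect sizes or variances.

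The consequence is confined to the load main effect and the simple load effects built on it. They cannot be separated from block, and even after block is removed they measure load together with practice, fatigue and session drift. A shift common to short and long sentences cancels from the interaction.

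The trial-number issue is secondary and conditional. If numbering is session-wide, the standard error of load rises by up to about a factor of 2 when trial-level noise dominates, and by less when by-subject load slopes are substantial. If numbering restarts in each block, there is essentially no loss.

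**What to change.** 1. Delete block from all main and exploratory models. This costs one line in the model formula.
2. State that the load main effect, and the simple load effects used to read analysis 4, are load plus order, because load always comes second and no covariate can fully separate the two. This costs a sentence or two in the plan and in the interpretation.
3. Fix the numbering of trial in advance and give the reason. Position within block (1–74, centred) keeps the precision of load but leaves session drift in the load effect. Session-wide numbering (1–148) adjusts for linear drift at a variance inflation of about 4 for load. One could be primary and the other a sensitivity analysis. This costs one recoded variable.

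None of these needs new data. Only varying the order of load across participants would separate load from order. Block would then be estimable and could stay in the models, but that changes the experiment and must be decided before data collection.

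### Constancy of the sentence-final low F0 is to be judged by finding no Sentence Length effect at p<0.05, and a non-significant result does not show constancy

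*Protocol article*

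**What the plan says.** In the Statistical analysis section of the Protocol article, the four outcomes "are modelled with separate linear mixed-effects regression analyses". The decision rule is common to all of them: "The significances of the main effects and the interaction are determined at the threshold of p<0.05".

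The model for sentence-final F0 minima has a particular job. "The third analysis checks the preliminaries of advance planning of sentence intonation"; more precisely, "the aim is to test how constant the sentence-final low F0 is in the elicited sentences". The next sentence gives the result that would meet this aim: "For this, the statistical evaluation should find no effect of Sentence Length". The same paragraph allows final F0 to rise under high load. It states no equivalence margin, smallest difference of interest, confidence-interval criterion or Bayes factor.

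The Participants section sizes the study for detecting effects: "given the small to medium effect size (d = 0.45), the recommended sample size of 60 subjects is suitable". The power claimed there is 0.8, and it covers each main effect as well as the interaction of all three factors. It was computed with "variation parameters set to PANGEA defaults".

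**The concern.** The aim is to show that something does not vary, but the tool is a test built to detect variation. A p-value above 0.05 can mean that the length effect is negligible, or that it was estimated too imprecisely to be seen. The rule cannot separate the two, and it favours imprecision: the noisier the F0 minima and the more trials are lost, the easier the desired result becomes. Both are realistic here. The Design section describes F0 as highly variable. The section on pre-processing excludes trials on gaze, fluency, syntax and latency, and removes a subject only when the inclusion rate is below 25%.

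At stake is part of the interpretation. The Introduction and the section on advance planning of sentence intonation use the stable final low as support for reading initial-peak height as planned in advance. The premise is also open for this language: the Protocol article reports that an earlier Estonian corpus study did not find constant low F0 at the ends of speech chunks. The check could therefore fail, and it needs a criterion able to tell constancy from lack of information.

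**Working it through.** **Inputs.** From Participants: d = 0.45, power 0.8, 60 subjects, 84 after inflation. From Statistical analysis: threshold 0.05 (two-sided is my assumption). From Design: 64 target pictures per subject. Sentence Length corresponds to the Identity factor, one of the three main effects covered by the power statement.

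**The plan's own figure.** The power of 0.8 cannot be reproduced exactly, because the default variance components are not listed. As a plausibility check, set total variance to 1, with item share v_i, subject-slope share v_s and residual v_e:

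SE = √(4·v_i/64 + 4·v_s/60 + 4·v_e/(60·64))

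With assumed shares of 0.30, 0.10 and 0.60, SE = √(0.01875 + 0.00667 + 0.00063) = 0.161, the ratio 0.45/0.161 is 2.79, and power is about 0.80. Over item shares of 0.05 to 0.40 and slope shares of 0.02 to 0.20, power runs from 0.63 to above 0.99. The stated 0.8 is attainable but cannot be verified. I take it as true below.

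**Implied precision.** In SD units:

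- 60 subjects: SE = 0.45/(1.960 + 0.842) = 0.161
- 84 fully usable subjects, best case (all of the error shrinks with the number of subjects): SE = 0.161 × √(60/84) = 0.136

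**Chance of finding no length effect** when the true effect is δ: P = Φ(1.96 − δ/SE) − Φ(−1.96 − δ/SE).

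| True δ (SD) | 60 subjects | 84, best case |
|---|---|---|
| 0 | 95% | 95% |
| 0.10 | 90% | 89% |
| 0.20 | 76% | 69% |
| 0.30 | 54% | 40% |
| 0.45 | 20% | 9% |

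For example, at δ = 0.20 with 60 subjects, δ/SE = 1.245, and Φ(0.715) − Φ(−3.205) = 0.762.

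**What a non-significant estimate leaves open.** An estimate near zero has a 95% interval of about ±1.96 × 0.161 = ±0.31 SD (±0.27 with 84).

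**Equivalence test instead.** With two one-sided tests at 0.05 each and margin m, power at a true zero is 2·Φ(m/SE − 1.645) − 1, or zero if that is negative. The document gives no margin, so a range is shown.

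| Margin m (SD) | 60 subjects | 84, best case |
|---|---|---|
| 0.45 | 0.75 | 0.90 |
| 0.30 | 0.18 | 0.43 |
| 0.20 | 0 | 0 |

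The smallest margin with 80% power is SE × (1.645 + 1.282), about 0.47 SD with 60 subjects and 0.40 SD with 84.

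**The case against.** The strongest reply is that the sentence states a prediction and not an acceptance rule. It sits among other predictions, and nowhere does the document say that p>0.05 will be reported as proven constancy. That is fair as to wording. But the sentence is tied directly to the aim of testing constancy and no other criterion is offered, so anyone following the text would count a non-significant result as support.

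A second reply is that nothing is conditional on this check. That stands. The fourth analysis tests Cognitive Load by Sentence Length on initial peaks whatever the third one shows. The article also gives another ground for advance planning, namely that peak height anticipates utterance length, and it proposes its working-memory account because the low-pitch limit leaves data unexplained.

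A reader might also infer more than the figures support:

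- *Constancy would readily be accepted even if valleys varied as much as peaks.* No peak effect is given, and d = 0.45 is not tied to one outcome. If it were the peak effect, an equal valley effect would be missed only about 20% of the time (9% with 84 usable subjects).
- *A trivial difference could overturn the premise.* At this precision, significance needs an estimate of about 0.31 SD, which is not trivial beside 0.45.
- *A non-significant result is compatible with 0.63 SD.* That is the outer 95% limit of an estimate lying exactly on the significance boundary (2 × 1.96 × 0.161). It is an extreme, not the typical case.

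**Conclusion.** The point holds as a weakness in how one supporting analysis is to be read. The stated criterion cannot establish constancy: no effect is the likelier result at true length effects of 0.20 SD (76%) and 0.30 SD (54%) with 60 subjects, and at 0.20 SD (69%) with 84. Protection is reasonable only near the effect size for which the study was planned.

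The sizes rest on taking the stated power as true for F0 minima, on a normal approximation and on a two-sided test. If the minima are noisier than the default variances imply, the chance of missing a real effect is higher; if less noisy, lower. That non-significance is not evidence of constancy does not depend on these numbers.

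A reader might infer that the main result is undermined. The document does not support that: what is affected is the support this check lends to the advance-planning interpretation.

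**What to change.** Before data are seen, fix a margin in semitones within which a length difference in sentence-final F0 would count as constant, and give the reason for it. The minima are already to be converted to semitones. The document gives no SD in that unit, so the SD margins above cannot be converted from it. Then:

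- Report the Sentence Length effect on F0 minima in semitones with its confidence interval.
- Claim constancy only if the 90% interval lies wholly inside the margin (two one-sided tests at 0.05).
- Otherwise report constancy as not established, and do not read p>0.05 as confirmation.
- Say whether the margin applies to the effect averaged over load or within each load level, since final F0 is allowed to differ by load.

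This needs no extra subjects or recordings, only revised wording and one pre-set margin. The real cost is that constancy becomes materially harder to claim. At a true zero the chance of supporting it falls from 95% under the present rule to about 75% with a 0.45 SD margin and 18% with 0.30 SD (90% and 43% with 84 fully usable subjects). A 0.45 SD margin is as large as the whole design effect, so the study can support only a loose constancy claim, and the report should say so.
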